### Additional information collected at baseline

Demographic and cancer diagnosis data will be collected from all participants at baseline. Participants will be asked to state the average number of hours they spend exercising in an average week before involvement in the study using the General Practioner’s Activity Questionnaire.

### Sample size

Sample size for the study was calculated based upon previously published data [37,38] and Cohen’s Power Primer [74]. According to a prospective calculation, for a repeated measures ANOVA, 26 participants per group are required to detect a large effect size with power of 0.80 and α set at .05. It is reasonable to assume a large effect size in this population based upon previous research [37,38] and their memory performance on the digit span. Allowing for 20% attrition due to withdrawal and illness we aim to recruit 31 patients per group.

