### Recruitment

Sixty two females with a primary diagnosis of breast cancer will be recruited from the Leicester Royal Infirmary (31 participants per group). Patients who have been diagnosed, are waiting to begin adjuvant or neo adjuvant chemotherapy and are considered fit to take part in moderate intensity exercise by their oncologist will be invited to participate in the study by the researcher. Oncologists will subjectively assess patients’ suitability for the study based upon their medical history and physical presentation during the consultation. Those interested in participating then meet with the researcher who will provide them with an information sheet and explain the study in further detail. Those participants who show interest are then followed up a week later at which point they are asked to complete a consent form. Participants will be assessed using objective measures of cognitive functioning in a small room near the waiting area. They will also complete a series of self-report questionnaires in the comfort of their own homes and return them using the pre-paid envelope provided.

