### Randomisation

Eligible participants will be block randomised using four blocks to ensure equal numbers of patients in both groups as recruitment will be staggered. Within each group of four patients, two will be allocated to the intervention group and two to the control group at time two (mid way through chemotherapy). There is no masking of participants or the research team.

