### Procedure

The researcher will recruit participants, collect cognitive and psychosocial data at pre and post-intervention and facilitate the delivery of the physical activity intervention. Initially, consenting participants will be asked by the researcher to complete a self-report cognitive functioning questionnaire, a battery of objective tests of cognitive impairment and a questionnaire pack assessing quality of life and emotional well-being pre-chemotherapy to allow familiarisation with the researcher and research materials. They will be asked to wear ActiGraph GT3X+ accelerometers for 10 hours a day for 7 days for a measure of habitual walking after the familiarisation assessment [63]. These data will be collected prior to receiving chemotherapy.

After completing two cycles of chemotherapy, participants will be asked to complete the same measures again at the clinic. Patients will then be randomised to either the intervention or control group following the procedures outlined above. The walking intervention starts after 2 cycles of treatment in line with recommendations from oncologists who suggests that the intervention will be better received by patients after they have had 2 cycles of chemotherapy and understand what they are facing with regard to treatment side effects. The intervention group will be asked to commit to the 12 week walking intervention and will be provided with a booklet outlining the amount of walking they should take part in alongside guidance and tips on how to incorporate this into their daily routines. The intervention group will also be asked to commit to a minimum of 150 minutes of moderate intensity walking per week for the duration of the 12 week intervention, in line with recommended guidelines [61]. They will be told how to monitor their own intensity levels and will be encouraged to aim to walk at moderate levels of intensity for 150 minutes a week for the duration of the intervention. Walking schedules will be self-prescribed by participants but the researcher will recommend that they begin by completing 10 minutes of walking at any one time and then steadily increase the duration of walking to 30 minutes. Participants will be provided with a pedometer for the duration of the intervention and will be asked to log their walking for the 12 week period. Those randomised to the control group will continue to receive usual care alone.

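### The 20% attrition allowance was multiplied on instead of divided out: 31 per group less 20% leaves 24.8, not the required 26

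*Protocol article*

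**What the plan says.** The Sample size section of the protocol article gives the requirement as "26 participants per group are required to detect a large effect size with power of 0.80 and α set at .05". It names a repeated measures ANOVA as the basis and gives no numerical effect size and no sidedness. It then makes the allowance: "Allowing for 20% attrition due to withdrawal and illness we aim to recruit 31 patients per group". The Recruitment section carries the same target forward: "Sixty two females with a primary diagnosis of breast cancer will be recruited", stated there as 31 in each group.

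Three places fix the timing. Under Recruitment, the women approached "are waiting to begin adjuvant or neo adjuvant chemotherapy". Under Procedure, "After completing two cycles of chemotherapy, participants will be asked to complete the same measures again at the clinic", and randomisation follows that assessment. Under Randomisation, of each four patients "two will be allocated to the intervention group and two to the control group at time two (mid way through chemotherapy".

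**The concern.** Three figures stand side by side in one section: 26 needed at the end, 20% expected to be lost, and 31 to be recruited per group. Any two of them determine the third, and the third as printed does not follow. An attrition rate is a fraction of the women who start, so the starting number is found by dividing the final number by the fraction retained. The 31 looks as if 20% of the final number had been added instead.

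At stake is whether the trial has the power it claims under the loss it expects itself. The 26 leaves little slack: on the assumptions set out in the working, it is the smallest number per group that reaches 0.80.

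A related uncertainty is what 31 per group counts. Women are recruited before chemotherapy, but groups exist only after two cycles.

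**Working it through.** **Inputs from the protocol article**
- Required at final assessment: 26 per group, 52 in total (Sample size).
- Power 0.80, α 0.05, a large effect (Sample size).
- Attrition 20% (Sample size).
- Target 31 per group, 62 in total (Sample size; Recruitment).

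**Assumptions, not in the document**
- Large is taken as a standardised difference d = 0.8.
- The test is two-sided.
- Power is computed for a two-sample t-test from the noncentral t distribution. In a 2×2 mixed design without covariates, the group-by-time test is equivalent to a two-sample t-test on the change score, so this is a reasonable stand-in. The planned cognitive analyses also adjust for age and menopausal status, which is not modelled here.

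**Step 1. Reproduce the 26.** On these assumptions, power is 0.791 at 25 per group and 0.808 at 26. The smallest number reaching 0.80 is 26, as stated.

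**Step 2. Reproduce the 31.** 26 × (1 + 0.20) = 31.2, rounded down to 31.

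**Step 3. Correct inflation.** 26 / (1 − 0.20) = 32.5, so 33 per group and 66 in total. On the total, 52 / 0.8 = 65, which becomes 66 with equal groups. Check: 33 × 0.8 = 26.4, which keeps 26. By contrast, 32 × 0.8 = 25.6, which does not.

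**Step 4. What 31 delivers.** 31 × 0.8 = 24.8 per group, and 62 × 0.8 = 49.6 in total against 52. The attrition at which 31 still leaves 26 is (31 − 26)/31 = 5/31 = 16.1%.

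Steps 2 to 4 need no effect size and no test.

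**Step 5. Power**

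| Completers per group | Power, d = 0.8 | Power, d = 0.792 |
|---|---|---|
| 26 | 0.808 | 0.800 |
| 25 | 0.791 | 0.784 |
| 24.8 | 0.788 | 0.780 |
| 24 | 0.774 | 0.766 |

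The last column sets d so that 26 gives exactly 0.80. In either column, moving from 26 to 24.8 costs about 0.02 in power.

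**Step 6. Starting point of the 20%.** If it runs from recruitment, 49.6 of 62 women remain. If it runs from randomisation and all 62 are randomised, the same 49.6 remain. The arithmetic error is therefore present on either reading. The document does not say which is meant.

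**The case against.** The best defence of the figure is that 20% means 20% of the 26 required: 26 + 5.2 = 31.2, which agrees with 31 after rounding. But attrition ordinarily means a share of those who enter and leave. The women who withdraw or fall ill come from the 31, so this reading explains how the figure arose without making it correct.

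A second defence is the intention-to-treat analysis named under Statistical analyses. It does not supply the missing post-intervention scores, and the Sample size section treats attrition as something to allow for.

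A third is that the consequence is slight. That stands: 1.2 women per group below requirement, and power near 0.79 in place of 0.80.

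A reader might also infer more: that the 20% is wrongly applied to women recruited before chemotherapy, so that losses in the first two cycles come on top and push the trial well below 24.8 per group. The article does not support this. It gives no starting point for the 20%, which may cover all loss from consent to final assessment, and counting from recruitment is then legitimate. The target is also expressed per group, so it can be read as women randomised. Larger shortfalls appear only if an assumed early loss is added to the full 20%: 10% before and 20% after randomisation would leave 62 × 0.90 × 0.80 / 2 = 22.3 per group (power 0.743). If the 20% already includes early loss, that counts the same women twice. With 10% lost in each period, 62 × 0.90 × 0.90 / 2 = 25.1 per group remain (power 0.793). No such rates are in the document.

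**Conclusion.** The point holds as an arithmetic error within the Sample size section. The stated 26, 20% and 31 cannot all be true: at 20% attrition the target must be 33 per group, and 31 per group tolerates at most 16.1%. This rests only on the article's own figures, and nothing elsewhere in the article repairs it.

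The size is small: 1.2 completers per group short (2.4 in total), and power of about 0.79 at 24.8 per group. The power figures depend on the assumed d = 0.8 and two-sided test, which reproduce the 26. The error does not threaten the validity of the trial; it is worth correcting because the correction is nearly free.

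Whether 31 per group means women recruited or women randomised is unclear from the Recruitment, Randomisation and Procedure sections. That calls for a clarifying sentence and does not demonstrate a further shortfall.

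**What to change.** Make one of two changes in the Sample size section.

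1. Keep 31 and restate what it gives: *31 per group keeps 26 evaluable with up to 16% attrition; at 20% attrition about 25 per group remain and power is about 0.79.* The sponsor should confirm the power from its own calculation and state the effect size and sidedness used. This costs one sentence and no patients.
2. Keep 20% and 26, and set the target to 33 per group (66 in total) in both the Sample size and Recruitment sections. This costs four more women than the present 62.

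With either change, add a sentence saying whether the per-group target counts women recruited or women randomised after two cycles, and whether the 20% includes loss before randomisation. The sentence itself is free. If the sponsor decides that the target counts women randomised and that recruitment continues until it is reached, the cost depends on early loss, which the article does not give. With an assumed early loss of 5% to 10%, randomising 62 would need 62/0.95 = 65.3, so 66, to 62/0.90 = 68.9, so 69, women recruited.

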### Statistical analyses

Quantitative data will be entered into Statistical Package for the Social Sciences (SPSS) and intention to treat analysis will be used in line with the CONSORT statement. To test the effectiveness of the physical activity intervention on cognitive function, a series 2x2 mixed ANCOVAs will be carried out controlling for age and menopausal status (controlling for natural differences in cognitive function associated with age and menopausal status). Participant group (intervention or control) will be entered as the between subjects factor and time (pre-intervention and post-intervention) will be entered as the within subjects factor. In addition, to test the effectiveness of the intervention on quality of life and measures of well-being another series of 2x2 mixed measures ANOVA will be carried out between the intervention group and control group. Post-hoc analysis will be carried out using a series of t-tests to check for differences between the intervention and control group. Lastly, to test whether emotional distress mediates between amount of physical activity (duration of walking and steps taken) and self-report cognitive functioning for the intervention group, a series of mediation analyses will be carried out using regression analyses.

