### Design

The study is a randomised controlled trial comparing the home based walking intervention group with care as usual control group. Outcomes will be assessed at two time points: mid-way through chemotherapy (pre-intervention) and after the completion of chemotherapy (post-intervention). All participants will also complete outcome measures prior to receiving chemotherapy to familiarise them with study materials, study setting and the researcher.

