### Outcome measures

All outcome measures will be completed at three time points: baseline (familiarisation), mid way through chemotherapy (pre-intervention) and after the completion of chemotherapy (post-intervention). All outcome measures have been validated in this population.

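### The 2x2 group-by-time analyses are change-score tests that do not use the pre-intervention score as a covariate: valid under randomisation, but less precise than the same data allow

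*Protocol article*

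**What the plan says.** For cognition, the Statistical analyses section states that "a series 2x2 mixed ANCOVAs will be carried out controlling for age and menopausal status". The two arms form the between-subject comparison. The repeated factor has two levels, for the section says that "time (pre-intervention and post-intervention) will be entered as the within subjects factor". For quality of life and well-being, "another series of 2x2 mixed measures ANOVA will be carried out between the intervention group and control group", with no covariate named. Follow-up comparisons are then described: "Post-hoc analysis will be carried out using a series of t-tests to check for differences between the intervention and control group".

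On timing, the Procedure section places the second assessment after two chemotherapy cycles and then says: "Patients will then be randomised to either the intervention or control group following the procedures outlined above". The pre-intervention score therefore precedes allocation. The Outcome measures section adds an earlier measurement: "All outcome measures will be completed at three time points: baseline (familiarisation), mid way through chemotherapy (pre-intervention) and after the completion of chemotherapy (post-intervention". The Design section gives that first measurement one purpose: "All participants will also complete outcome measures prior to receiving chemotherapy to familiarise them with study materials, study setting and the researcher". It has no role in the efficacy models.

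**The concern.** In the planned models the pre-intervention score is one level of the outcome. It is not an adjustment variable. The treatment test therefore subtracts the whole pre-intervention score from the post-intervention score, whatever the correlation between them. When the correlation is moderate, this subtracts too much and adds noise. Regression on the pre-intervention score estimates how much to subtract.

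The trial has little power to spare. The Sample size section plans 26 analysed per group for 80% power at a large effect. Recruiting 31 and losing 20% leaves 31 × 0.8 = 24.8, about 25. An efficiency gain from data already collected is worth having in a trial of this size.

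**Working it through.** **Inputs.** From the Sample size section: 26 per group, power 0.80, alpha 0.05, large effect. From Statistical analyses: two time levels, with age and menopausal status as covariates for cognition. Assumptions: two-sided alpha; large effect taken as d = 0.8; equal pre and post variances (SD = 1); r varied, since the document gives none.

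**The plan's own figure.** An exact two-sided two-sample t-test at d = 0.8 needs 25.5, so 26 per group, with power 0.807 at 26. The stated 26 is reproduced.

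**Equivalence.** A two-time-point mixed model with age and menopausal status (each also crossed with time) was fitted to test data beside a regression of change on group, age and menopausal status. Both gave t = -0.15699 for the treatment effect.

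**Variance of the treatment effect** (per-arm units of SD²):
- planned change-score test: 2(1 - r)
- post score adjusted for pre score: 1 - r²
- ratio: (1 - r²) / [2(1 - r)] = (1 + r)/2

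At N = 52 with two other covariates and group in the model, the extra covariate multiplies the adjusted variance by 1 + 1/(52 - 1 - 3) = 49/48. Power uses the noncentral t with noncentrality 0.8/√(2v/26), where v is the variance above, on 48 df (planned) or 47 df (adjusted).

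| r | 2(1 - r) | 1 - r² | ratio | ratio after df cost | power, planned | power, adjusted |
|---|---|---|---|---|---|---|
| 0.5 | 1.00 | 0.75 | 0.75 | 0.77 | 0.81 | 0.90 |
| 0.7 | 0.60 | 0.51 | 0.85 | 0.87 | 0.95 | 0.98 |
| 0.8 | 0.40 | 0.36 | 0.90 | 0.92 | 0.99 | 1.00 |

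In 5,000 simulated trials per value of r, the variance ratios were 0.76, 0.87 and 0.90. Power went from 0.79 to 0.89 at r = 0.5 and from 0.94 to 0.97 at r = 0.7. Both estimators averaged close to the true 0.8.

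**Adding the pre-chemotherapy score.** The result depends on how it correlates with the other two.
- Equal correlations on all three occasions: variance 1 - 2r²/(1 + r), which is 0.667, 0.424 and 0.289 at r = 0.5, 0.7 and 0.8. Relative to the planned test this is 0.67, 0.71 and 0.72, an extra 8, 14 and 18 percentage points beyond the one-covariate model.
- Correlation 0.7 between adjacent occasions and 0.6 between first and last: R² = (0.49 + 0.36 - 2 × 0.7 × 0.6 × 0.7)/(1 - 0.49) = 0.262/0.51 = 0.514. The variance is 0.486, and 0.486/0.60 = 0.81. The total cut is 19%, only 4 points beyond the 15% from one covariate.
- AR(1) decay (first-to-last correlation r²): the partial correlation given the pre-intervention score is zero, so nothing is added.

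**The case against.** The strongest reply is that nothing in the plan is wrong. Under randomisation the change-score estimate is unbiased, and its standard error already covers chance imbalance at the pre-intervention assessment. That stands: this is lost efficiency, not bias.

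The gain also has limits. In general the advantage of adjustment is (SD_pre - r·SD_post)², which vanishes when r = SD_pre/SD_post. With equal variances, the df cost cancels it at (1 + r)/2 × 49/48 = 1, that is at r of about 0.96. So it would be too strong to say that adjustment wins at every correlation below 1. At r = 0.7 and the planned effect, the power gain is only about 0.02. A cut of about 30% from using both earlier scores needs equal correlations on all three occasions. The pre-chemotherapy test is the most distant and was taken for familiarisation, so a weaker correlation is plausible.

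A reader might infer three further faults that the text does not support:
- **That the group main effect, which averages in a pre-randomisation score, is the treatment test.** The Abstract defines the primary outcome as change in Digit Span, so the interaction is the natural reading.
- **That the post-hoc t-tests compare groups at the pre-intervention assessment.** No time point is given for them.
- **That leaving age and menopausal status out of the well-being models is an error.** The plan justifies those covariates by their link to cognition, so the omission follows from its own reasoning.

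**Conclusion.** The point holds as a matter of efficiency. The planned tests are valid change-score tests that leave out a covariate measured before randomisation. Adjusting for the pre-intervention score would cut the variance of the effect by about 25% at r = 0.5, 15% at r = 0.7 and 10% at r = 0.8, or 23%, 13% and 8% after the degree of freedom. This rests on equal pre and post variances and on assumed values of r. In power, the gain is material at r = 0.5 (0.81 to 0.90) and small at r = 0.7 (0.95 to 0.98). The pre-chemotherapy score may help further, but the document gives no basis for fixing the amount.

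**What to change.** For every cognitive and well-being outcome, regress the post-intervention score on group and pre-intervention score, with age and menopausal status kept for the cognitive outcomes. Report the adjusted group difference with its 95% CI as the treatment effect, in place of the interaction test and the unadjusted post-hoc t-tests.

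The pre-chemotherapy score may be added as a second covariate. If it is, state how a missing value is handled so that no participant leaves the analysis because of it. This matters because the questionnaires are completed at home and posted back.

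The cost is one degree of freedom (two with the second covariate), a rewritten analysis paragraph, and a sample-size sentence that names the new model. No new data, visits or software are needed. A complete-case fit loses nobody further for a missing pre-intervention score, since the change score already requires it.

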## Methods

### Objectives/hypothesis

The primary aim of the study is to investigate the effectiveness of a home-based moderate intensity walking intervention on reducing cognitive impairment of breast cancer patients receiving chemotherapy. Our primary hypothesis is that women who complete the physical activity intervention will demonstrate less impairment in memory in comparison to women in the non-intervention group. Our secondary hypotheses are that the intervention group will perform better than the control group on objective and subjective measures of cognitive function, and will report better quality of life outcomes than the control group. Furthermore, within the intervention group, emotional well-being will mediate between physical activity level and level of subjectively reported and objectively tested impairment in memory, attention and concentration.

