Post-intervention (after the completion of 6 cycles of chemotherapy), all participants will be asked to wear the accelerometer for a further 10 hours a day for 7 days. In addition, they will be asked to complete the same questionnaires and neuropsychological tests as those completed at pre-chemotherapy and mid way through chemotherapy. At the end of the study the control group will receive the intervention booklet (see Figure 1 for flow chart of study methods).

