### Measures of physical activity

Accelerometers (motion sensors which detect accelerations produced by the human body), will be worn by all participants for 10 hours a day for 7 days at baseline and post-intervention to assess habitual physical activity [63]. Pedometers will be worn by participants randomised to the intervention group for 10 hours a day for the duration of the twelve week intervention in order to record frequency of steps taken. They will also complete the Borg Rating of Perceived Exertion Scale [64] and The Talk Test [65] to subjectively monitor the intensity of their walking during the intervention.

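### The mediation hypothesis is tested by an unadjusted regression on self-prescribed walking in about 25 women, and only for self-reported cognition although objective outcomes are also hypothesised

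*Protocol article*

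**What the plan says.** Under Objectives/hypothesis, a secondary hypothesis confined to the intervention group is that "emotional well-being will mediate between physical activity level and level of subjectively reported and objectively tested impairment in memory, attention and concentration".

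Under Statistical analyses, the last analysis takes duration of walking and steps as exposure, emotional distress as mediator, and as outcome "self-report cognitive functioning for the intervention group, a series of mediation analyses will be carried out using regression analyses". The Abstract likewise mentions self-reported cognition only. Age and menopausal status are named as covariates for the cognitive ANCOVAs; none is named for the mediation models.

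The Procedure leaves the walking schedule to the participant, and the Intervention section asks her to plan her goals around her treatment cycles. Steps, duration and intensity are recorded during the programme by pedometer and diary, in the intervention arm.

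The only sample-size statement concerns the group comparison: "for a repeated measures ANOVA, 26 participants per group are required". On recruitment it adds: "Allowing for 20% attrition due to withdrawal and illness we aim to recruit 31 patients per group".

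**The concern.** Allocation is randomised, but the amount walked within the walking arm is not. A woman with a heavier symptom burden may walk less, feel more distressed and report more cognitive failures. The article itself makes this plausible: it describes patients on chemotherapy as often unwell, ties walking goals to treatment cycles, and links psychosocial well-being to cognitive decline. An unadjusted regression of cognition on walking and distress cannot separate that common cause from a pathway that runs from walking through distress to cognition.

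A positive finding could therefore be read as a mechanism when it reflects illness severity. A negative finding would carry little information at this sample size. In addition, the objectively tested half of the stated hypothesis has no analysis.

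**Working it through.** **1. The plan's own figure.** The article gives 26 per group for a large effect, power 0.80 and α 0.05. Taking large as d = 0.8 (an assumption; no number is given) and a two-sided two-sample t-test, power = P(|T| > t(0.975, 2n−2)) with noncentrality 0.8·√(n/2). This gives 0.791 at n = 25 and 0.807 at n = 26, so 26 reproduces. It covers the between-group comparison only, and no power is claimed for mediation.

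**2. Size of the mediation set.** 31 × (1 − 0.20) = 24.8, about 25 women.

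**3. What 25 women can detect.** The smallest single correlation with 80% power (Fisher z) is r = tanh[(1.960 + 0.842)/√(25 − 3)] = tanh(0.597) = 0.535.

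For mediation I simulated the joint-significance test: walking→distress, and distress→cognition given walking, each at two-sided p < 0.05. Paths are standardised, there is no direct effect, and 20,000 trials were run per row. The path sizes are assumptions.

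| Both paths | Power, n = 25 |
|---|---|
| 0.3 | 8% |
| 0.4 | 22% |
| 0.5 | 45% |

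**4. What confounding alone can produce.** Assume one illness factor with loading λ on distress and on cognitive complaints, −λ on walking, and no effect of any of the three on another. Every pairwise correlation then has size λ². The apparent path from walking to distress is −λ². The apparent path from distress to cognition given walking is (λ² − λ⁴)/(1 − λ⁴) = λ²/(1 + λ²). Their product is a spurious indirect effect:

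- λ = 0.5: −0.25 × 0.25/1.25 = −0.050
- λ = 0.6: −0.36 × 0.36/1.36 = −0.095
- λ = 0.7: −0.49 × 0.49/1.49 = −0.161

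The rate of falsely declared mediation at n = 25 (20,000 trials each), without adjustment and with adjustment for pre-intervention distress, fatigue and cognition, is below. The pre-intervention values load on the illness factor in the same way, and the factor is taken as stable over the programme.

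| λ | Unadjusted | Adjusted |
|---|---|---|
| 0 | 0.2% | 0.2% |
| 0.3 | 0.4% | 0.3% |
| 0.5 | 3% | 0.8% |
| 0.6 | 10% | 1% |
| 0.7 | 25% | 1% |

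Stability matters. At λ = 0.6, if illness before and during the programme correlates at 0.7 instead of 1, the adjusted rate is 3.7%; at a correlation of 0.5 it is 5.4%. Adjustment reduces the problem and does not abolish it.

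**5. Price of the adjustment.** Three covariates take the outcome model from 25 − 3 = 22 to 25 − 6 = 19 residual degrees of freedom. If they explained nothing, power at paths of 0.4 would fall from 22% to about 17%.

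**6. Outcomes side by side.** Objectives/hypothesis names subjectively reported and objectively tested outcomes; Statistical analyses names self-report only. The mediator also shifts. It is emotional well-being in the hypothesis, which is a heading over several scales in the measures section. In the analysis it is emotional distress, which the measures section assigns to one of those scales, the shortened Profile of Mood States.

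**The case against.** The analysis matches its hypothesis in one respect: the hypothesis is itself framed within the intervention group. The mediation models are secondary and listed last, the randomised contrast is already the main analysis, and no power is claimed for mediation. Covariates for a secondary model are often left to a fuller document. All of this stands, and it limits the weight of the point. It does not make self-prescribed walking an unconfounded exposure, and the mismatch in outcomes lies in the article's own text.

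The confounding figures depend on the assumed loading. At 0.5 or below, false mediation stays at about 3% or less, so low power is the firmer numerical point.

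Three stronger readings are tempting, and the documents do not support them.

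- A reader might infer that the accelerometer schedule causes the problem, or that activity in both arms is measured only after the programme. The device "will be worn by all participants for 10 hours a day for 7 days at baseline and post-intervention to assess habitual physical activity", the first wear being before chemotherapy, and everyone also reports usual exercise at baseline. The planned exposure is logged during the programme, so accelerometer timing has no bearing on the confounding.
- A reader might infer that contamination of controls cannot be checked. Their walking during the 12 weeks is indeed unmeasured, but the two wears give an indirect check. Moving the second wear would trade away the post-programme week of habitual activity.
- A reader might infer that allocation should replace walking as the exposure. That answers a different question, without walking dose, and distress remains non-randomised. With 50 women, a loading of 0.6, a group effect on distress of d = 0.5 and no effect of distress on cognition, group-based mediation is falsely declared in about 30% of simulated trials unadjusted. With pre-intervention mediator and outcome adjusted for, the rate is still roughly 10 to 14%, depending on the simulation run.

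**Conclusion.** The point holds as a weakness of a secondary analysis. As written, the mediation test is an unadjusted, single-arm regression on a self-chosen exposure in about 25 women. It would miss mediation with paths of 0.4 in roughly four trials out of five. Under a strong common illness factor (loading 0.6 to 0.7) it would falsely declare mediation in about 10% to 25% of trials; under a moderate one (0.5 or less), in about 3% or fewer. These sizes rest on assumed paths and loadings, a joint-significance test and 20% attrition.

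Separately, and without any assumption, the objectively tested part of the hypothesis has no planned mediation analysis. The randomised comparison of the primary outcome is untouched.

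**What to change.** 1. In Statistical analyses, adjust the within-arm mediation regressions for the pre-intervention values of emotional distress, fatigue and the cognitive outcome being modelled. Outcome measures has all of these collected mid-way through chemotherapy, before the programme, so no new data are needed.
2. Label these models exploratory, and state that walking dose is not randomised.
3. Make the two sections agree: either run the same models for the objectively tested memory and attention outcomes, or narrow the hypothesis to self-report. Name the same mediator in both places.
4. Optionally, add a model in all randomised women (group→post-intervention distress→post-intervention cognition, adjusted for the pre-intervention mediator and outcome). It would complement the walking-dose models, not replace them, and its remaining mediator–outcome confounding should be stated.

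The cost is wording plus three degrees of freedom per model, which is noticeable at 25 women. Running the objective outcomes adds further tests, which is another reason for the exploratory label.
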